**Figure 1 figure1:**
[figure not shown]
The study design. SES: socioeconomic status.

**Table 1 table1:** Overview of intervention.

	A (control group)	B (intervention group)
Participants, n	44	44
Name of medication	Navak Guggulu	Vachaharidradi Gana Vati
Dosage	Young’s formula	Young’s formula
Frequency	Thrice a day before meals	Thrice a day before meals
Duration	90 days	90 days
Assessment	1st, 15th, 30th, 45th, 60th, 75th, and 90th day	1st, 15th, 30th, 45th, 60th, 75th, and 90th day
Follow-up	180th day	180th day
Route of administration	Oral	Oral
Anupana	Lukewarm water	Lukewarm water

The Suryanamaskara techniques following the Bihar School of Yoga Tradition will be advocated to the children [36,37]. Each participant will be provided with detailed written instructions, provided in local language, outlining the Ayurvedic diet restrictions as follows: avoid eating all sweet food items (chocolate, ice creams, etc), potatoes, dairy products (paneer, curd, cheese, Shrikhand, etc), fried foods (wafers, puri, and pakora), and bakery products (biscuits, pastries, cakes, bread, etc); refrain from consuming junk foods and fast-food items; avoid sweetened soft drinks and beverages; and avoid overeating and eating without hunger and ensure appropriate intervals between meals. Patients will be given regular reminders also through calls or SMS text messages to follow diet restrictions and perform Suryanamaskara. SPIRIT (Standard Protocol Items: Recommendation for Interventional Trials) guidelines will be used for the study.

### Inclusion Criteria

The inclusion criteria are as follows: participants irrespective of gender, religion, and socioeconomic status, age group between 10 and 16 years with signs and symptoms of overweight (Sthaulya) due to exogenous causes, participants with BMI ≥23 and <27 kg/m^2^, and parents who are willing to provide written informed consent for their children to be included in the study.

### Exclusion Criteria

The exclusion criteria are as follows: children having BMI <23 and ≥27 kg/m^2^, children aged <10 years and those aged >16 years, and children who are overweight due to endocrine causes. Children experiencing severe systemic illnesses like hypertension, asthma, diabetes mellitus, nephrotic syndrome, kwashiorkor, and congestive cardiac failure having anasarca condition are overviewed as overweight.

### Drug Collection or Authentication

The raw material for the both the control and intervention drugs will be purchased from a reliable source and will be authenticated and identified by the department of Dravyaguna and Rasashastra of Mahatma Gandhi Ayurved College Hospital and Research Centre, Salod, Wardha.

### Details of Drug Composition and Preparation Method

The control drug is Navak Guggulu, which is a polyherbal compound mentioned in Yogaratnakara [38]. It has been proven to have antiobesity effects in many randomized controlled trials (RCTs). The composition of Navak Guggulu is presented in Table 2.

**Table 2 table2:** Latin name and family name of the herbs used in Navak Guggulu.

Serial No	Drug	Latin name	Family
1	Shunthi	*Zingiber officinale*, Roscoe	Zingiberaceae
2	Pippali	*Piper longum*, Linn	Piperaceae
3	Marich	*Piper nigrum*, Linn	Piperaceae
4	Haritaki	*Terminalia chebula*, Retz	Combretaceae
5	Bibhitaki	*Terminalia bellirica*, Roxb	Combretaceae
6	Amalaki	*Emblica officinalis*, *Phyllanthus emblica*, Linn	Euphorbiaceae
7	Musta	*Cyperus rotundus*	Cyperaceae
8	Chitrak	*Plumbago zeylanica*, Linn	Plumbaginaceae
9	Vidanga	*Embelia ribes*, Burm	Myrsinaceae
10	Guggulu	*Commiphora mukul* or *Balsamodendron mukul*, Hook	Burseraceae

### Preparation Method of Navak Guggulu

In the Good Manufacturing Practice (GMP)–certified pharma company, guggulu will be first purified by dissolving in Triphala kwatha (decoction), and then, the decoction will be filtered and concentrated by heating it. In that concentration, the remaining herbs in the form of fine powder will be mixed well. Then, this mass will be dried in the drying machine. With the help of a punching machine, tablets of 300 mg will be made. Each tablet of Navak Guggulu approximately contains 150 mg of pure guggulu and 16.66 mg of remaining herbs each.

The intervention drug is Vachaharidradi Gana mentioned by Acharya Vagbhata in his classic Ashtanga Hridaya [39]. It has the opposite qualities to Kapha and Meda. Keeping this fact in mind, selected herbs from Vachaharidradi Gana were selected for oral use in children with overweight in the modified form of tablet (vati). The selected drugs are detailed in Table 3, and their preparation process is shown in Figure 2.

**Table 3 table3:** Latin name and family name of the herbs used in Vachaharidradi Gana Vati.

Serial No	Drug	Latin name	Family
1	Vacha	*Acorus calamus*, Linn	Araceae
2	Musta	*Cyperus Rotundus*, Linn	Cyperaceae
3	Devdaru	*Cedrus deodara* or *Pinus deodara*, Roxb	Pinaceae
4	Shunthi	*Zingiber officinale*, Roscoe	Zingiberaceae
5	Haritaki	*Terminalia chebula*, Retz	Combretaceae
6	Haridra	*Curcuma longa*, Linn	Zingiberaceae
7	Daruharidra	*Berberis aristata*, DC	Berberidaceae

**Figure 2 figure2:**
[figure not shown]
Preparation method of Vachaharidradi Gana Vati. GMP: Good Manufacturing Practice.

The process of trituration is a part of the Ayurvedic pharmaceutical concept known as Bhavana. It enhances the bioavailability of the active compounds. Each tablet of Vachaharidradi Gana Vati contains approximately 50 mg of each herb, along with 5 mg of decoction of each herb. The quality control of the final products will be assessed by analyzing both the raw materials and final products of both drugs in a GMP-certified pharmacy.

### Criteria for Assessment

#### Objective Parameters

The anthropometrical parameters, weight, BMI, waist circumference, abdominal girth, mid-arm circumference, waist-hip ratio (WHR), and triceps skinfold thickness (TSFT), will be measured before and after treatment.

#### Instruments and Techniques Required for Anthropometric Data Collection

Children’s weight will be measured with an electronic portable scale with high sensitivity and specificity and will be calibrated from time to time. Height will be measured by portable stadiometers, with the participants’ feet placed together with heels, buttocks, and shoulder blades against the stick and head positioned in the Frankfurt horizontal plane. Waist and hip circumferences will be measured twice using inextensible anthropometric tape, with the children standing erect and relaxed with arms at the sides and feet positioned close together. Waist circumference will be measured midway between the lowest border of the rib cage and the upper border of the iliac crest, at the end of normal expiration [40].

Hip circumference will be measured at the widest part of the hip at the level of the greater trochanter. Mid-upper arm circumference will be taken at midpoint of the tip of the acromion process to the olecranon process, with the tape slung to the skin but not compressing the soft tissues. Both right and left sides will be measured, and the average will be taken [41].

For all measurements, the tape will be positioned at a level parallel to the floor. All measurements will be in centimeters to the nearest 0.1 cm, except TSFT. TSFT will be measured in millimeters at the midpoint between the tip of the acromion process and the olecranon process (back side of the middle upper arm) with the help of the calibrated skinfold caliper. BMI will be calculated as the ratio of body weight to the square of height (kg/m^2^), and WHR will be calculated as the ratio of waist to hip circumference [42]. Proper training will be provided to the personnel for accurate measurements using these techniques.

#### Investigations Proposed

Hemoglobin percentage, thyroid-stimulating hormone, and random blood sugar are the screening tests to be done only before treatment, whereas lipid profile will be done to assess the efficacy of interventions before treatment as well as after treatment. These laboratory tests will be performed using standard equipment and gold standard methods to ensure accurate results.

#### Subjective Parameters

Signs and symptoms of obesity (Sthaulya) are mentioned in the Ayurvedic texts, and for assessing the severity of each symptom, they were graded following the book called WHO-Direct Financial Cooperation sponsored project on Developing Guidelines for Clinical Research Methodology in Ayurveda. It is illustrated in Table 4 [43].

**Table 4 table4:** Signs and symptoms of Sthaulya according to Ayurvedic classics.

Signs and symptoms or gradation	0	1	2	3	4
Pendulous hips, abdomen, breasts (chala sphika, udara, stana)	Absence of movements (in the areas) (Chalatva)	Little visible movement (in the areas) after rapid movement	Little visible movement (in the areas) after moderate movement	Movement (in the areas) after mild movement	Movement (in the areas) after changing posture
Bad odor (angagandha)	No odor	Bad odor but not offensive	Strong odor but can be lessened by the use of deodorants and perfumes	Very strong odor even after using fragrances (use of deodorants or perfumes)	—^a^
Perspiration (swedadhikya)	Sweating after heavy work and fast movement or in hot weather	Profuse sweating after moderate work and movement	Sweating after little work and movement (stepping ladder)	Profuse sweating after little work and movement	Sweating even at rest or in cold weather
Increased appetite (kshudha-adhikya)	As usual or routine	Slightly increased (1 meal extra with routine diet)	Moderately increased (2 meals extra with routine diet)	Markedly increased (3 meals extra with routine diet)	—
Increased thirst (pipasa-adhikya)	Feeling of thirst (7-9 times or 24 hours) and relieved by drinking water	Feeling of moderate thirst (>9-11 times or 24 hours) and relieved by drinking water	Feeling of excess thirst (>11 times or 24 hours) and not relieved by drinking water	Feeling of severe thirst (>13 times or 24 hours) and not relieved by drinking water	—
Exertional dyspnea (kshudra shwasa)	No dyspnea even after heavy work	Dyspnea after moderate work but relieved later and tolerable; dyspnea by climbing upstairs of 10 steps, and time taken will be more than 15 seconds	Dyspnea after little work but relieved later and tolerable; dyspnea by climbing upstairs of 10 steps, and time taken will be more than 25 seconds	Dyspnea after little work but relieved later and not tolerable; dyspnea by climbing upstairs of 10 steps, and time taken will be more than 35 seconds	Dyspnea in resting condition
Increased sleep (nidradhikya)	Normal and sound sleep for 6-8 hours or 24 hours with a feeling of lightness and relaxation in the body and mind	Sleep>8-9 hours with slight heaviness in the body	Sleep>9-10 hours or 24 hours with heaviness in the body associated with yawning (Jrimbha)	Sleep>10 or 24 hours with heaviness in the body associated with yawning (Jrimbha) and sleepiness (Tandra)	—

^a^Not applicable.

### Participants

It is crucial to calculate the effect size according to the equivalence or superiority formula with the help of the SD and mean difference of the reference paper [44]. This approach enhances the RCT, making it superior to other types of research. In this study, an attempt is made to assess the equivalence effect of Vachaharidradi Gana Vati against the standard controlled drug, Navak Guggulu. The equivalence formula is applied, and the sample size is calculated to minimize any bias. So, the formula for equivalence (parallel design) has been used to calculate the sample size of this study. For that, the reference values of the control drug have been used [44].

The formula for equivalence (parallel design) is:

where *Z*_α_=1.96, α=type I error at 5%, σ=SD, *Z*_β_=0.84 (for equivalence 2-tailed), β=type II error at 20%, and δ=true differences in means.

Sample size (N) = *n*1 = 2 × (1.96 + 0.84)^2^ × (0.86)^2^/(0.57)^2^ = 39 each

Total=78 samples. With 10% dropout=43 each=86 samples.

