## Methods

### Study Design

A randomized, standard-controlled, double-blind equivalence clinical trial will be performed. The study flow is depicted in Figure 1. The study participants required for the trial include children with overweight aged between 10 and 16 years of age will be selected from the Outpatient Department and Inpatient Department of the Department of Kaumarbhritya, Mahatma Gandhi Ayurveda College Hospital and Research Centre, Salod (H), and Chhatrapati Shahu Maharaj Shikshan Sanstha’s (CSMSS) Ayurved College and Hospital, Chhatrapati Sambhajinagar, based on the inclusion criteria.

Overweight (Sthaulya) children will be diagnosed as having a BMI greater than or equal to 23 and less than 27 kg/m^2^ [11]. Screening will include hemoglobin percentage, thyroid-stimulating hormone, and random blood sugar. A total of 88 diagnosed children with overweight will be selected after obtaining written informed consent from their guardians. Participants will be randomly divided into 2 groups by block randomization using a computerized random number generator or statistical software. Group A (control group) will receive Navak Guggulu, while group B (trial group) will receive Vachaharidradi Gana Vati orally (Table 1). Medications will be dispensed in opaque containers following the sequentially numbered, opaque, sealed envelope (SNOSE) technique to maintain allocation concealment. Both groups will receive counseling to perform 12 Suryanamaskara (Sun Salutation) per day and adhere to the dietary restrictions. Guardians will be educated and advised to support their children’s consistent participation in the interventions. All the baseline parameters will be recorded at the study’s initiation. The treatment duration will be 90 days, with follow-up assessments on the 15th, 30th, 45th, 60th, 75th, and 90th day to monitor progress and ensure adherence. Lipid profile will be assessed before treatment and on the 90th day of intervention to evaluate the efficacy of the interventions. An additional follow-up will occur on the 180th day to determine whether the intervention’s possible effects are lasting.

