### Justification on the Formula

The equivalence formula for parallel-group design is particularly suitable for this study, as it is specifically designed to determine the sample size needed to assess whether 2 interventions—Vachaharidradi Gana Vati and Navak Guggulu—are statistically equivalent within a defined margin of clinical acceptability. This approach is crucial for trials aimed at establishing equivalence rather than superiority or noninferiority. The formula accounts for the population variability in the population by incorporating the SD of the control drug and ensures a robust comparison by considering both type I and type II error rates, set at 5% and 20%, respectively. This balance between the risks of false-positive and false-negative results is critical in equivalence trials, where even small differences may have clinical significance.

By including the true difference in means (δ), the formula ensures that the calculated sample size is adequate to detect equivalence within the predefined margin. The adjustment for a 2-tailed test reflects the bidirectional nature of equivalence testing, ensuring that the study is powered to detect differences in either direction. Given these attributes, this formula provides a scientifically robust framework for calculating the required sample size, ensuring that the study’s conclusions about equivalence are statistically valid and clinically meaningful. The sample size ensures that each participant receives individualized care and monitoring.

For reference values, a clinical trial paper was used [44].

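### The printed sample-size line gives 36 per arm, not 39, and its Z values, error rates and n cannot all hold for an equivalence trial with an unnumbered margin

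*Protocol article*

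**What the plan says.** Under Study Design the protocol article declares the aim: "A randomized, standard-controlled, double-blind equivalence clinical trial will be performed". The Hypotheses section accordingly takes non-equivalence as the null.

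The Participants section says that the parallel-design equivalence formula is used, with Z(alpha) = 1.96 for a 5% type I error. It defines the remaining terms as "0.84 (for equivalence 2-tailed), β=type II error at 20%, and δ=true differences in means". The substituted line is "2 × (1.96 + 0.84)^2^ × (0.86)^2^/(0.57)^2^ = 39 each", followed by "With 10% dropout=43 each=86 samples". Randomization and Allocation Sequence Generation then raises the total to 88, or 44 per arm.

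Justification on the Formula repeats the 5% and 20% error rates and again calls delta the true difference in means. In the same sentence it says that "the formula ensures that the calculated sample size is adequate to detect equivalence within the predefined margin". It adds: "The adjustment for a 2-tailed test reflects the bidirectional nature of equivalence testing". No number in the article is labelled as the margin. No confidence level for concluding equivalence is given.

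**The concern.** Three things do not fit together.

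- **Arithmetic.** The printed inputs do not give the printed result.
- **Method.** Pairing 1.96 with 0.84 is the usual recipe for detecting a difference of size delta with a two-sided 5% test. For equivalence with no true difference, two one-sided tests must both succeed, so beta is split and 0.84 becomes 1.28.
- **Meaning of delta.** In an equivalence calculation the divisor is the margin less the assumed true difference. If 0.57 were both the margin and the true difference, the treatments would by definition not be equivalent.

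What is at stake is which confidence interval may support the primary conclusion, and whether the stated 80% power goes with it. A reader who takes 1.96 at face value will expect a 95% interval, and the planned size does not give 80% power under that rule.

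**Working it through.** **Inputs from the article.** Z(alpha) = 1.96, Z(beta) = 0.84, SD = 0.86, delta = 0.57, n = 39 per arm and 10% dropout (Participants); 44 per arm finally (Randomization and Allocation Sequence Generation).

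**Assumptions needed for equivalence power.** 0.57 is the margin (the only candidate number) and the true difference is 0. The article states neither.

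**1. The printed line.**
2 × (1.96 + 0.84)² × 0.86² / 0.57² = 2 × 7.84 × 0.7396 / 0.3249 = 35.69, so 36 per arm.
Rounding of the inputs does not rescue 39. SD 0.865 with delta 0.565 gives 36.8, and SD 0.855 with delta 0.575 gives 34.7. A t-based version of the same difference test gives 36.7, so 37.

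**2. What does give 39.**
n = 2 × SD² × (Z(1−alpha) + Z(1−beta/2))² / margin²

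| Z(alpha) | Z for beta | n per arm | rounded up |
|---|---|---|---|
| 1.96 | 0.84 (as printed) | 35.69 | 36 |
| 1.645 | 1.28 | 38.95 | 39 |
| 1.96 | 1.28 | 47.79 | 48 |

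The second row is the equivalence formula with 5% in each one-sided test and beta of 20% split in two.

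**3. Equivalence power at the planned size.**
SE = SD × √(2/n). At a true difference of 0, power = 2 × Φ(margin/SE − Z(alpha)) − 1.
For n = 39: SE = 0.86 × √(2/39) = 0.1948 and 0.57/0.1948 = 2.927.
- Z = 1.645: 2 × Φ(1.282) − 1 = 80.0%
- Z = 1.96: 2 × Φ(0.967) − 1 = 66.6%

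With the SD estimated and the t distribution used, the figures are slightly lower:

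| Evaluable per arm | 90% interval: normal / t | 95% interval: normal / t |
|---|---|---|
| 39 | 80.0% / 79.1% | 66.6% / 64.8% |
| 44 | 85.7% / 85.0% | 74.9% / 73.6% |

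**4. If the true difference is not 0.** By the normal approximation with 39 per arm and Z = 1.96, power is about 60% at a true difference of 0.1 and 45% at 0.2. At a true difference equal to the margin, the chance of declaring equivalence is only the one-sided error rate: 5% with a 90% interval, 2.5% with a 95% interval.

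**5. Dropout.** 39 × 1.1 = 42.9, which is the article's 43. Dividing instead, 39/0.9 = 43.3, so 44 per arm and 88 in total, which is the size adopted.

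**The case against.** The strongest reply is that the sample size is right and only the printed Z values are wrong. The article states error rates of 5% and 20%. Two one-sided tests at those rates give exactly 39 per arm, with power of about 80%. The formula itself did not survive in the text at hand, so only the substituted numbers can be judged. This reply stands as far as it goes: a misprint fits the text at least as well as a wrong method. It does not remove the defect, because the line as published is false and nothing in the article says which element should give way.

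A reader might go further and infer that the trial was sized with a superiority formula, so that its 80% power is really 65%. The documents do not support that. The difference formula would have given 36, not 39, and 65% applies only if a 95% interval decides equivalence, which no section fixes.

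A second fair point is that 0.57 as the margin and 0 as the true difference are not in the article. The Participants section says the values come from a reference paper on the control drug, which is not available here. Reproducing 39 does not make 0.57 a justified margin, so the authors must supply and defend these values.

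Nor is the dropout step a separate error, since the final 44 per arm covers 10% loss from 39.

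**Conclusion.** The point holds in this form. The printed calculation is wrong (35.7, so 36 per arm, against 39). Its Z values are those of a two-sided difference test in a trial declared to be an equivalence trial. Delta is labelled the true difference although the argument needs a margin, and that margin has no number. The printed Z values, the error rates and n cannot all be correct together.

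The loss of power is conditional. With margin 0.57, SD 0.86 and true difference 0, power is about 79% (39 evaluable per arm) to 85% (44) under a 90% interval rule, and about 65% to 74% under a 95% rule. It is lower in every case if the true difference is not 0. The plan is therefore adequately sized on one reading and short of its stated 80% on the other, and the article does not say which applies.

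**What to change.** State three things: the equivalence margin (confirming and justifying 0.57 on clinical grounds if that is the margin), the assumed true difference, and the confidence level that decides equivalence. Stop labelling delta the true difference if it is the margin. Then correct the line in one of two ways.

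- **90% interval rule.** Print Z = 1.645 and Z(beta/2) = 1.28. With margin 0.57 and true difference 0 this gives 39 per arm and, at 39/0.9, 44 per arm. The planned 88 stands.
- **95% interval rule.** Keep Z = 1.96 and 88 children, and restate power as about 65% (39 evaluable per arm) to 74% (44) in place of 80%.

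Either is a change of text and adds no participants. The second gives up the 80% claim; holding 80% with a 95% interval would need 48 evaluable per arm, or 48/0.9 = 53.3, so 54 per arm with dropout. If the margin or the assumed difference turns out to be something else, the calculation must be redone. The choice should be recorded before the treatment codes are broken.

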### Justification on the Formula

The equivalence formula for parallel-group design is particularly suitable for this study, as it is specifically designed to determine the sample size needed to assess whether 2 interventions—Vachaharidradi Gana Vati and Navak Guggulu—are statistically equivalent within a defined margin of clinical acceptability. This approach is crucial for trials aimed at establishing equivalence rather than superiority or noninferiority. The formula accounts for the population variability in the population by incorporating the SD of the control drug and ensures a robust comparison by considering both type I and type II error rates, set at 5% and 20%, respectively. This balance between the risks of false-positive and false-negative results is critical in equivalence trials, where even small differences may have clinical significance.

By including the true difference in means (δ), the formula ensures that the calculated sample size is adequate to detect equivalence within the predefined margin. The adjustment for a 2-tailed test reflects the bidirectional nature of equivalence testing, ensuring that the study is powered to detect differences in either direction. Given these attributes, this formula provides a scientifically robust framework for calculating the required sample size, ensuring that the study’s conclusions about equivalence are statistically valid and clinically meaningful. The sample size ensures that each participant receives individualized care and monitoring.

For reference values, a clinical trial paper was used [44].

